#### Cost-effectiveness

The economic evaluation will be a cost-utility analysis from a societal perspective, based on patient reports and with a 1-year time horizon (without discounting). The analysis will be very similar to the analysis performed for the lumbosacral radicular syndrome [34].

Group averages will be compared using double-sided bootstrapping and costs will be compared to patient outcome using net-benefit analysis. An integral cost–price analysis will be performed to estimate operating costs. Other health care costs will be valued using standard prices [35], including time and travel costs. Absenteeism will be valued using both the friction-cost method (primary analysis) and the human-capital method. Quality-adjusted life years (QALYs) will be estimated using the EQ5D (primary analysis, Dutch tariff), the SF6D and the patients’ health state utility VAS (transformed to a utility scale using the power transformation U = 1-(1-VAS/100)^1.61^) [36].

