### Baseline data

The baseline questionnaires and demographics will be registered before randomisation. Also the preferences of patients and doctors will be registered using a 5-point scale varying from ‘strong preference for surgery’ to ‘strong preference for conservative treatment’.

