9. EuroQol – EQ-5D. The EuroQol (EQ-5D) will be used to value the patients’ health for the cost utility analysis. As indicated by the name the tool measures five dimensions: mobility, self-care, daily activities, pain/discomfort, and anxiety/depression. Each domain is rated as having no problems, some problems or extreme problems.

10. Cost diaries, including absenteeism, will be filled out by the patients during follow-up.

11. MRI. MRI findings at baseline and after 1 year will be compared: extrusion or protrusion, the difference in size of the disc herniation, nerve root compression, and, if operated, presence of scar tissue will be registered. The data will be registered using standardised CRFs, which will be filled out by the local radiologist and neurosurgeon.

12. Frequency of (re)operation in the conservative group and frequency of reoperation in the surgery group.

13. Frequency of complications.

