#### Secondary outcome

Secondary outcomes will be analysed for differences between groups with linear mixed models similar to the main endpoint. Furthermore, we will investigate whether potential prognostic variables (gender, age, presence of neck pain, more neck pain than arm pain, Valsalva manoeuvre test, Spurling test, shoulder abduction test, type of personality based on DS-14 and based on IPQ-K, anterior or posterior approach, smoking, neurological deficits (strength on an 1–5 Medical Research Council (MRC) scale and sensibility), duration of the symptoms, Quetelet index) are associated with the difference between the treatment arms in the primary endpoint. This will be carried out by adding a potential prognostic variable and its interaction with the treatment arm to the linear mixed model.

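### The economic analysis names no adjustment for intake utility; as written, the QALY difference is valid but less precise than the collected data allow

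*Protocol article*

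**What the plan says.** The protocol article's Cost-effectiveness section describes a cost-utility analysis "based on patient reports and with a 1-year time horizon (without discounting"). The effect measure is fixed by instrument: "Quality-adjusted life years (QALYs) will be estimated using the EQ5D (primary analysis, Dutch tariff), the SF6D and the patients’ health state utility VAS". The comparison between arms is one sentence: "Group averages will be compared using double-sided bootstrapping and costs will be compared to patient outcome using net-benefit analysis". No covariate is named. The section also refers to an earlier analysis for its approach: "The analysis will be very similar to the analysis performed for the lumbosacral radicular syndrome [34"].

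The intake values exist. The Baseline data section says "The baseline questionnaires and demographics will be registered before randomisation", and Table 2 marks EuroQol, SF-36 (the source of the SF-6D) and the health state utility VAS at intake.

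The Secondary outcome section has a general model, "Secondary outcomes will be analysed for differences between groups with linear mixed models similar to the main endpoint", and EQ-5D is on the list of secondary outcomes. The article does not carry that model over to QALYs or net benefit, for which the Cost-effectiveness section sets its own method.

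**The concern.** Intake utility contributes to a QALY in two ways if the QALY is the area under the utility curve: it is the first point of that area, and it correlates with later points. In an unadjusted comparison, a chance difference between arms at intake therefore stays in the QALY difference and passes into net benefit. Adjustment for the intake value removes most of that chance component and narrows the interval, using data the trial already collects.

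This matters somewhat more here than in a trial expecting a large effect. The Discussion expects comparable pain at one year and better cost-effectiveness for prolonged conservative care, so a small QALY difference is plausible. Changing the mixed model for VAS arm pain would not help, because the QALY analysis uses a different outcome and a different baseline variable.

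**Working it through.** **The plan's own figure.** The only stated figure used is 200 per arm, from the Sample size section. Its formula, with σ = 30/25 = 1.2 and Δ = 4/12 mm per month, gives n = (1.96 + 0.84)² × 2 × 1.2² / (4/12)² + 1 = 204.2, against 200 stated. That agrees within 3%. The article gives no utility SD, between-visit correlation or target QALY difference.

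**Assumptions (not in the documents).** The QALY is a trapezoid area over the Table 2 visits to one year. Utility SD is the same at each visit, taken as 0.25 where a value is needed. Intake correlates a with every follow-up visit, and follow-up visits correlate b with each other. Unadjusted power is set at 80%.

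**Weights.** At 0, 6/52, 0.25, 0.5, 8/12 and 1 year the weights are 0.058, 0.125, 0.192, 0.208, 0.250 and 0.167. The text under Outcome assessment has a 9-month visit where Table 2 has 8 months; using 9 months changes the variance cut by one percentage point or less at the correlations checked (0.3, 0.5 and 0.7).

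**Formulas, in units of SD².**
- Slope of QALY on intake utility: c = 0.0577 + 0.9423a.
- QALY variance: v = 0.0577² + 2 × 0.0577 × 0.9423a + 0.9423²b + 0.1863(1 − b), where 0.1863 is the sum of the squared follow-up weights.
- Share of variance removed by adjustment: r² = c²/v. This does not depend on the SD.
- Adjusted power: Φ(2.80/√(1 − r²) − 1.96).

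Example with a = 0.2, b = 0.5: c = 0.2462, v = 0.5622, r² = 0.0606/0.5622 = 0.108.

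| a (intake to follow-up) | b (among follow-up) | c | v | variance cut | power, from 80% |
|---|---|---|---|---|---|
| 0.1 | 0.1 | 0.152 | 0.271 | 9% | 83% |
| 0.2 | 0.2 | 0.246 | 0.352 | 17% | 87% |
| 0.3 | 0.3 | 0.340 | 0.433 | 27% | 91% |
| 0.5 | 0.5 | 0.529 | 0.595 | 47% | 97% |
| 0.1 | 0.5 | 0.152 | 0.551 | 4% | 82% |
| 0.2 | 0.5 | 0.246 | 0.562 | 11% | 84% |
| 0.3 | 0.5 | 0.340 | 0.573 | 20% | 88% |

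**Effect of an imbalance.** At SD 0.25 and 200 per arm, the SE of the intake difference is 0.25 × √(2/200) = 0.025. A 1-SE imbalance shifts the unadjusted QALY difference by c × 0.025: 0.004, 0.006, 0.009 or 0.013 for a = 0.1, 0.2, 0.3 or 0.5. A 2-SE imbalance, roughly a 1-in-20 event, doubles that. The SE of the unadjusted QALY difference is 0.25 × √(2v/200), which is 0.013 to 0.019 over these rows. The direct route through the first point is minor (0.058 × 0.025 = 0.0014); nearly all of the shift comes through the correlation with later visits.

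**Net benefit.** Costs add variance that this adjustment does not remove. As an illustration only: if costs supply half the net-benefit variance and are independent of QALYs, the cut is r²/2. For a = b = 0.2 that is 8.6%, and power is 83% where the QALY alone reaches 87%.

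**The case against.** The strongest objection is that the lack of adjustment is inferred. The article never calls the averages raw and does not exclude covariates. A bootstrap of group averages says how uncertainty is obtained and is compatible with an adjusted difference in each resample. The article is condensed, and its method follows an earlier analysis that is not shown. This stands in part: adjustment may be intended. But the comparison method is stated, its plain reading is unadjusted, and the section goes into detail on the tariff, the absenteeism methods and the utility transformation.

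Second, nothing is invalid. A reader might infer that the QALY result would be biased, or that its interval would be wrong. The documents do not support that: under randomisation the unadjusted difference is unbiased, and its interval already allows for chance intake variation. This objection stands in full.

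Third, the size is uncertain. Equal correlation across visits probably flatters adjustment, because patients enter on a threshold of 40 mm, symptoms are expected to fall sharply, and treatment begins after intake. This also stands, which is why the table includes lower intake correlations.

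Fourth, a reader might infer that the net-benefit conclusion would turn on an intake imbalance, or that the main question of the trial is at risk. The QALY figures do not show the first, since cost variance dilutes the effect. On the second, the Background puts (cost-)effectiveness in the primary goal, but the Abstract and the Discussion list costs and cost-effectiveness as secondary.

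**Conclusion.** The point holds as an efficiency improvement in how the economic comparison is specified. Under the stated assumptions, adjustment for intake utility cuts the variance of the QALY difference by about 4% to 20% in the more cautious case and 9% to 47% under equal correlation. At the low end the gain is negligible (80% to 82% power); at the high end it is substantial. The documents give no correlation that would place the trial within this range, and the gain for net benefit is smaller by an amount that depends on the cost variance. The article contains no error on this point, and the full protocol or an economic analysis plan may already settle it.

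**What to change.** In the Cost-effectiveness section, state that patients are resampled with their costs and QALYs kept together and that, in each resample, the QALY is regressed on treatment arm and the intake utility from the same instrument: intake EQ-5D for the primary analysis, intake SF-6D and intake utility VAS for the other two. Use the adjusted arm difference for the QALY comparison and for net benefit, and report the unadjusted difference as a sensitivity analysis.

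The cost is one or two sentences and a few lines of code, with no new data, patients or procedures. The downside is that the main QALY difference no longer equals the simple difference of the two reported means, so both should be shown. If adjustment is already intended, one clause saying so is enough.

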### Development CRS questionnaire

The participants will also participate in the development and validation of a functioning scale for CRS: the Leiden Cervical Radicular Syndrome Functioning (LCRSF) scale. This questionnaire will combine arm pain, neck pain, and motor and sensory deficits. A secondary aim is to build a prediction model predicting SF-6D and EQ-5D utilities from the LCRSF scale.

### Timeline

Ethics approval was obtained in May 2012 from the Human Research Ethics Committee of the Leiden University Medical Center. Approval from the participating hospitals occurred during May 2012 – now. Recruitment of participants commenced in August 2012. All participants are expected to have completed the study by the summer of 2016.

## Conclusion and Discussion

The objective of the current trial is to study the effectiveness of the surgical intervention and prolonged conservative care for CRS. Secondary, an analysis of cost-effectiveness, timing of surgery and prognostic factors in favour of one of the strategy arms will be performed. The only two other randomised trials on this subject enrolled a limited number of patients and did not measure these secondary outcomes.

The CASINO trial is performed using ‘usual care’ and has a pragmatic design. It acknowledges that sometimes it may not be possible to postpone surgery for every conservative care patient until 6 months after allocation and that some patients will recover before surgery is performed in the surgical group. In these cases we consider it infeasible and unethical to hold on to the randomised treatment. Because of the intent-to-treat analysis, these cases will be analysed according to the originally allocated randomisation arm. Methodologically, this is the appropriate way to compare two healthcare strategies, as opposed to two treatments.

We hypothesise that prolonged conservative care will have comparable results as surgery on primary outcome (i.e. VAS pain or tingling sensations) after one year of follow-up. However, due to the risks and the costs of surgery we hypothesise that prolonged conservative care will be more (cost-) effective with less adverse events.

We hypothesise that those patients who endured symptoms for a longer time, would benefit from surgery. If true, it would be interesting to investigate whether there is a cut-off time-point after which surgery demonstrates a better result.

Finally, the predefined subgroup analyses may provide us with parameters, which can predict preference for one of the two treatment strategies. It is hypothesised that patients demonstrating more neck pain than arm pain or a type D personality will have better outcomes with conservative therapy.

The results of the present study will provide insight in the results of surgery at an early phase and of prolonged conservative care. This information will be useful in shared decision-making for choosing the most appropriate treatment for radicular cervical syndrome.

## Abbreviations

CRS: Cervical radicular syndrome; DS-14: Distressed personality questionnaire; GP: General practitioner; HNP: Hernia nuclei pulposus; IPQ-K: Illness perception questionnaire; MRC: Medical research council; MRI: Magnetic resonance imaging; NDI: Neck disability index; QALY: Quality-adjusted life year; RCT: Randomised controlled trial; SF-36: Short form-36; VAS: Visual analogue scale.
